#### 9.1.2 Secondary endpoints

1. Unrecognized chronic kidney disease, defined as elevated albuminuria, not reported by the subject and not previously recorded in electronic medical records of the subjects' general practice or pharmacy.
2. Persistent elevated albuminuria, defined as elevated albuminuria persisting despite good adherence to treatment with RAS-inhibitors for at least 6 weeks prior to elevated albuminuria assessment (score  $\geq 4$  on the Medical Adherence Report Scale (MARS)) (Appendix C, paragraph 16.3).
3. Change in frequency of cardiovascular risk factor monitoring, defined as the difference between the frequency of cardiovascular risk factor monitoring in participants 3 years before and 6 months after targeted albuminuria screening.
4. Changes in cardiometabolic drug prescriptions, defined as changes in any prescription for cardiovascular disease or CKD 6 months after targeted albuminuria screening compared to three years before.

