decades it has been shown that elevated albuminuria has a relatively high prevalence in patients with type 2 diabetes (20 – 40%), hypertension (15 – 25%) and the general population (5 – 9%) (2,3,9). As a result, the World Health Organization (WHO) has recently accepted elevated albuminuria as part of the definition of CKD (10). Current guidelines recognize albuminuria as central to CKD staging and provide criteria for referral and treatment (11). The prevalence of albuminuria in Dutch primary care subjects at risk of developing chronic kidney disease per risk group is currently unknown.

A progressive yearly deterioration of renal function is frequent in patients with diabetes and hypertension that results in elevated albuminuria (12). ACE-inhibitors (ACEi) and Angiotensin Receptor Blockers (ARBs) are recommended by clinical practice guidelines to lower albuminuria and blood pressure in patients with hypertension and diabetes (11). Despite the use of current therapies, the risk of developing CKD remains high (2). ACEi and ARBs reduce albuminuria by approximately 30%, leaving albuminuria not optimally controlled in many patients. To further optimize cardiovascular and kidney prognosis, Sodium Glucose co Transporter 2 (SGLT2) inhibitors, such as dapagliflozin, are a promising new class of therapy. SGLT2 inhibitors have been demonstrated to lower albuminuria and protect the kidney in patients with established chronic kidney disease (CKD) with or without diabetes (13). Whether this effect can be extended to a broader population of individuals at early stages of chronic kidney disease is currently tested in a randomized clinical trial.

Although albuminuria tests have been proven successful in identifying high-risk CKD patients, previous studies have shown that albuminuria measurements are only conducted in a minority of individuals at risk, even in high-risk groups (9). A study in England evaluated the prevalence of both recognized and unrecognized CKD in a study conducted at pharmacies that selected patients with CKD risk factors (Diabetes Mellitus, cardiovascular disease, history of CKD, hypertension, smoking). They reported that 113 of 720 (16%) patients with CKD risk factors had unrecognized CKD (14). A similar study in the United States found that among patients with type 2 Diabetes Mellitus more than half of the patients showed changes in renal markers indicating renal damage. However, only 12% of them had CKD documented in their chart review (4).

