#### 3.2 Secondary objectives

1. To estimate the prevalence of unrecognized chronic kidney disease in subjects with a high risk of chronic kidney disease in the Netherlands.
2. To estimate the prevalence of persistent elevated albuminuria under adequate treatment with renin-angiotensin system (RAS) inhibitors in subjects with a high risk of chronic kidney disease in the Netherlands
3. To assess frequency of cardiovascular risk monitoring by general practitioners after targeted albuminuria screening.
4. To assess changes in cardio-metabolic drug prescriptions after targeted screening.

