#### **4.2 Phase 2: Elaborated screening phase**

When there is no elevated albuminuria at phase 1, a letter with the results will be sent to the participant, and no further actions from the participant are required. Subjects will be carefully informed about the results.

When elevated albuminuria is confirmed ( $\geq 3.0$  mg/mmol on two occasions), subjects are invited for an elaborated screening visit with a researcher. At the start of the visit, participants will be asked to provide informed consent. Next, CKD/CVD risk factors will be assessed and the participant's medication use, and medication adherence will be reviewed during an interview. GPRI will produce a report of their findings which will be shared with the general practice, including recommendations for additional measurements or treatment changes if applicable.

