### Elaborated screening phase

In case of elevated albuminuria, subjects will be invited to attend an elaborated screening visit with a researcher of GPRI at the pharmacy, GP practice or other convenient location near the subject.

The following data will be collected by interview:

1. Medical history of
  - a. Kidney disease
  - b. Albuminuria
  - c. Diabetes Mellitus, type 1 or 2, including a history of keto-acidosis

- d. Cardiovascular disease
  - e. Hypertension
  - f. Lipid disorders
2. Medication use over the last 6 weeks
3. Medication adherence measured with the medication adherence report scale-5 (MARS-5) (appendix 16.3)
4. Smoking status, never, current, or ex-smoker

The following data will be collected by measurement:

1. Pulse rate
2. Systolic and diastolic tension (mean of 3 measurements)
3. Height
4. Weight (kg)
5. Creatinine and HbA1c in capillary blood

A report will be sent to the general practitioner based on these findings. The general practitioner will be advised to follow the NHG guidelines for cardiovascular management (Appendix 0) and to adjust treatment, if necessary.

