#### Evaluating non-response:

Aggregated data of characteristics from the total population of subjects that is eligible for screening will be collected from each general practice through VIPLive and will be combined to describe pooled characteristics of the total eligible population from general practices (Table 2).

*Table 2. Distribution of characteristics of the study population selected from participating general practices*

| Characteristic                         | Distribution              |
|----------------------------------------|---------------------------|
| Age                                    | Mean (standard deviation) |
| Sex, female                            | Number (%)                |
| Diabetes Mellitus                      | Number (%)                |
| Elevated albuminuria in last 11 months | Number (%)                |
| Lipid disorder                         | Number (%)                |
| Obesity                                | Number (%)                |
| Hypertension                           | Number (%)                |
| Cardiovascular disease                 | Number (%)                |
| Kidney disease                         | Number (%)                |

Pharmacies will be asked to provide similar data used to select their subjects.

The distribution of subject characteristics in the total selected population will be compared with the distribution among responders using collected information to evaluate occurrence of systematic response bias. Collected information of responders will be used for post-stratification and weighting methods to account for potential response bias in the estimation of prevalences (19).

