| Ernstige chronische nierschade:
eGFR < 30 of 30-44 met ACR 3-30; eGFR 45-59 met ACR > 30                                                                                                                                                                                                                                     |                                       |                                                            |                                                                       |                                             |                          |                           |                                                                             |
| Tienjaarsrisico op sterfte aan HVZ met SCORE ≥ 10%                                                                                                                                                                                                                                                                              |                                       |                                                            |                                                                       |                                             |                          |                           |                                                                             |
| Matige chronische nierschade:
eGFR 30-44 met ACR < 3; eGFR 45-59 met ACR 3-30; eGFR ≥ 60 met ACR > 30                                                                                                                                                                                                                        | < 2,6                                 | < 2,6 (overweeg medicatie bij voldoende levensverwachting) | Geen medicatie starten of stop lipidenverlagende medicatie            | < 140 (eventueel < 130*)                    | < 150 (eventueel < 140*) | < 150 en ≥ 70 diastolisch | Leefstijladvies

Overweeg medicamenteuze behandeling                  |

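### The endpoint called unrecognized chronic kidney disease counts only unrecognized albuminuria, so it cannot estimate the prevalence named in secondary objective 1

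*Protocol*

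**What the plan says.** Section 3.2 of the protocol gives the first secondary objective as "To estimate the prevalence of unrecognized chronic kidney disease in subjects with a high risk of chronic kidney disease in the Netherlands". The Summary has the same objective.

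Section 9.1.2 turns it into an endpoint: "Unrecognized chronic kidney disease, defined as elevated albuminuria, not reported by the subject and not previously recorded in electronic medical records" of the practice or pharmacy. The Summary gives the same albuminuria-only rule, but joins the two recognition conditions with *or* where section 9.1.2 has *and not*. Section 11 does not use the CKD label here. It speaks of unrecognized elevated albuminuria, reported as a percentage with a 95% confidence interval.

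On data collection, section 4.2 states: "When there is no elevated albuminuria at phase 1, a letter with the results will be sent to the participant, and no further actions" are asked of that person. The item "Creatinine and HbA1c in capillary blood" in section 9.3 belongs to the elaborated visit, which is offered only after confirmed albuminuria.

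On what CKD is, the Introduction says that the WHO has "accepted elevated albuminuria as part of the definition of CKD". Appendix B, section 16.2.2, lists "eGFR 30-44 met ACR < 3" under moderate chronic kidney damage.

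**The concern.** The title of the endpoint is wider than its rule. A percentage reported under the name of the objective would be read as the share of high-risk people with unrecognized CKD. The Introduction invites that reading, because it cites a pharmacy study in which 113 of 720 patients (16%) with risk factors had unrecognized CKD, and readers will set the two figures side by side.

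Two things could separate the reported figure from the one that the objective names. Kidney disease without albuminuria is left out, which pulls the figure down. Kidney disease that is already on record might be counted in, which would push it up. If both operate, the reader cannot tell the net direction.

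**Working it through.** The protocol states no figure that depends on this definition, so there is nothing to reproduce. The check is a comparison of sections, followed by an illustration of direction.

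**1. Can kidney disease with normal UACR be counted?**
- The case rule in section 9.1.2 requires elevated albuminuria and has no eGFR or diagnosis element.
- Subjects with a normal PeeSpot result leave after the letter (section 4.2), so the study takes no creatinine from them.
- Under section 11, practice patients with a recorded normal UACR in the previous 18 months enter the denominator without being invited. They are non-cases whatever their eGFR.
- Section 16.2.2 nevertheless classes eGFR 30-44 with ACR below 3 as moderate damage, and eGFR below 30 as severe with no ACR condition attached.

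Part of what the protocol itself calls chronic kidney damage therefore contributes zero cases by construction. An analysis plan cannot repair this from study measurements, because none exist for these people.

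**2. What must be unrecorded?** The sentence in section 9.1.2 allows two readings.
- *Albuminuria reading:* the elevated albuminuria was not reported or recorded. Section 11 supports this by its wording. So does the questionnaire in Appendix A, which asks about known protein in the urine and has no kidney-disease item.
- *CKD reading:* the comma lets the recognition conditions explain the word unrecognized in the title. The visit interview, which asks about kidney disease and albuminuria separately, is compatible with this.

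The choice matters because known kidney disease is not an exclusion (section 5.3), and because Table 2 in section 11 lists "Kidney disease" in a row separate from elevated albuminuria. A patient with recorded kidney disease and no recorded albuminuria is unrecognized on the first reading and recognized on the second.

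**3. Direction.** Let *a* be the share of truly unrecognized CKD that has no albuminuria, and *r* the share of counted cases whose kidney disease was already on record. If T is the true number, the correctly counted cases are (1 − a)T, and these make up a fraction (1 − r) of all counted cases. So

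reported / true = (1 − a) / (1 − r).

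The documents give neither value. With assumed ranges of 20-60% for *a* and 5-20% for *r*:

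| a | r | reported / true |
|---|---|---|
| 20% | 5% | 0.80 / 0.95 = 0.84 |
| 20% | 20% | 0.80 / 0.80 = 1.00 |
| 60% | 5% | 0.40 / 0.95 = 0.42 |
| 60% | 20% | 0.40 / 0.80 = 0.50 |

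The figure is too low when a exceeds r and too high when r exceeds a. On the CKD reading r is 0 and the ratio is 1 − a, here 0.80 to 0.40. These values show how the errors combine; they are not estimates.

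**The case against.** The strongest reply is that screening by albuminuria is an openly declared choice. The Introduction states it as the aim, the endpoint gives its operational definition in the same sentence as its name, and section 11 already reports under the narrower name. Someone who reads the definition knows what was counted. That stands as a defence of the design, which is not in dispute. It does not cover the objective and the endpoint title, which still promise a CKD prevalence.

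The reply also limits the point. A reader might infer four stronger things that the documents do not support:

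- *That the plan definitely counts known kidney disease as unrecognized.* It does so on one of two readings. That reading is the better supported, but the wording is ambiguous.
- *That the inflation is large, say 10 percentage points.* If an assumed 10% of cases had kidney disease on record, that would be 10% of cases, not 10 points of prevalence. With an assumed case prevalence of 5-20%, it is 0.10 × 5% = 0.5 to 0.10 × 20% = 2 points.
- *That participants with a normal result are told they have no CKD.* Sections 4.1 and 4.2 say only that they are informed of their result.
- *That the primary cost endpoint is affected.* Section 9.1.1 does speak of kidney disease there, but ties it to screening for albuminuria, and section 11 fixes the divisor as confirmed elevated albuminuria.

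**Conclusion.** The point holds for the label. As written, the study would report an albuminuria figure as a prevalence of unrecognized CKD. The omission of kidney disease with normal UACR is certain and complete, and follows from the case rule and from where creatinine is measured. The possible counting of already recorded kidney disease is conditional on the albuminuria reading.

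The size of either error, and so the net direction, cannot be derived from the protocol; the ratios above rest wholly on assumed shares. The consequence is confined to one descriptive secondary objective. It deserves correction because it decides what that objective can conclude, while both primary results stay as they are.

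**What to change.** 1. In the Summary and in sections 3.2 and 9.1.2, rename the objective and the endpoint as unrecognized elevated albuminuria, and add one sentence saying that it does not estimate total CKD.
2. State that a case is unrecognized only if neither elevated albuminuria nor kidney disease was reported by the subject or recorded. Apply this in the individual record check that the endpoint already requires, and in the visit interview.
3. Align the *or* in the Summary with the *and not* in section 9.1.2, and the kidney-disease wording of primary endpoint 2 in section 9.1.1 with confirmed elevated albuminuria in section 11.

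The cost is wording and one added condition, with no new measurement. The claim becomes narrower and the count possibly slightly smaller.

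There is one practical limit. For confirmed cases who do not attend the visit, the kidney-disease item depends on the record check. The questionnaire does not ask about it, Table 2 is aggregated, and the six-month extraction described in sections 4.3 and 9.3 covers only risk-factor monitoring and prescriptions. It should not be assumed that an existing extraction already holds this item for each person.

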#### Secondary endpoints

1. Unrecognized chronic kidney disease, defined as elevated albuminuria, not reported by the subject or previously recorded in electronic medical records of the subjects' general practice or pharmacy.
2. Persistent elevated albuminuria, defined as elevated albuminuria persisting despite good adherence (score  $\geq 4$  (doses seldom or never missed) reported in MARS) to treatment with RAS-inhibitors for at least 6 weeks prior to elevated albuminuria assessment.
3. Changes in frequency of cardiovascular risk factor monitoring, defined as the difference between the frequency of cardiovascular risk factor monitoring in participants 3 years before and 6 months after targeted albuminuria screening.
4. Changes in cardiometabolic drug prescriptions, defined as changes in any prescription for cardiovascular disease or CKD 6 months after targeted albuminuria screening compared to 3 years before.

**Nature and extent of the burden and risks associated with participation, benefit and group relatedness:** All selected subjects will be asked to participate on a free-will base and to send a signed informed consent form with a completed short questionnaire to GPRI. They will be

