## **5.4 Sample size calculation**

We aim to examine at least 112 patients with elevated albuminuria at the elaborated screening phase in this study. In the pilot study, 57 patients were examined at the elaborated screening phase. In the pilot study, 2 pharmacies and 3 general practitioners were included. For the extension, 3 pharmacies and 7 general practitioners will be recruited. We assume that at least 6300 patients from general practices and pharmacies will be eligible for inclusion in the screening phase.

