### 16.3 Appendix C: Medical Adherence Report Scale (MARS)

#### De Medication Adherence Report Scale – MARS test

De **Medication Adherence Report Scale (MARS)** is een meetinstrument voor therapietrouw waarbij 5 stellingen met de patiënt overlopen worden. Door het optellen van de score krijgt u een zicht op de therapietrouw: hoe hoger de score, hoe beter de therapietrouw. Bij een MARS-somscore van 21 of een score van 4 op elk individueel item wordt de patiënt als therapietrouw beschouwd.

|                                                        | Altijd
(score = 1)    | Vaak
(score = 2)      | Soms
(score = 3)      | Zelden
(score = 4)    | Nooit
(score = 5)     |
|--------------------------------------------------------|--------------------------|--------------------------|--------------------------|--------------------------|--------------------------|
| Ik vergeet mijn medicijnen te nemen                    |  |  |  |  |  |
| Ik wijzig de dosering van mijn medicijnen              |  |  |  |  |  |
| Ik stop een tijdje met het innemen van mijn medicijnen |  |  |  |  |  |
| Ik beslis een inname over te slaan                     |  |  |  |  |  |
| Ik neem minder dan voorgeschreven                      |  |  |  |  |  |

MARS-vragenlijst

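### Adherence to RAS inhibitors in secondary endpoint 2 is scored with MARS-5 statements about medicines in general, so users can be misclassified in either direction

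*Protocol*

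**What the plan says.** Section 9.1.2 of the Protocol defines secondary endpoint 2 as "elevated albuminuria persisting despite good adherence to treatment with RAS-inhibitors for at least 6 weeks" before the albuminuria assessment, and ties good adherence to a MARS score of at least 4, with a pointer to Appendix C. The Summary gives the same cut-off and explains it as "doses seldom or never missed) reported in MARS". Neither place says whether the 4 is an item score, a mean or a sum.

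The adherence data come from the elaborated screening visit. Section 9.3 lists among the interview items "Medication adherence measured with the medication adherence report scale-5 (MARS-5" and, separately, "Medication use over the last 6 weeks". Only people with confirmed elevated albuminuria reach that visit: Section 4.2 says that these "subjects are invited for an elaborated screening visit with a researcher".

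Appendix C prints the instrument. Its first statement is "Ik vergeet mijn medicijnen te nemen" (I forget to take my medicines). Three of the five statements refer to *my medicines*. The other two, on skipping an intake and on taking less than prescribed, name no medicine at all. The appendix also carries its own rule: "Bij een MARS-somscore van 21 of een score van 4 op elk individueel item wordt de patiënt als therapietrouw beschouwd", that is, a sum score of 21 or a 4 on each item.

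**The concern.** The endpoint needs to know how well one drug class is taken, but the instrument asks about the whole regimen. For someone whose only medicine is an ACE inhibitor or ARB the two coincide. For someone who also takes, say, a statin or a glucose-lowering drug they need not.

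Two errors follow, and they pull in opposite directions. A patient who takes the RAS inhibitor every day but often skips another drug can truthfully score low and leave the numerator. A patient who is careless only with the RAS inhibitor can answer for the regimen as a whole and stay in it.

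At stake is the meaning of secondary objective 2, which asks how much albuminuria persists under adequate RAS inhibition. Section 11 reports this as a percentage with a 95% confidence interval. That interval covers sampling error only. The instrument and its wording are fixed in the protocol, so no later analysis plan can recover drug-specific adherence from a general score.

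**Working it through.** The protocol states no expected value or precision for this endpoint. The 112 in Section 5.4 ("We aim to examine at least 112 patients with elevated albuminuria at the elaborated screening phase") comes without a formula, so there is no figure to reproduce. Three checks were made.

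**1. Does anything make the MARS score specific to the RAS inhibitor?** Section 9.1.2 attaches the score to RAS-inhibitor adherence. Section 9.3 names the MARS-5 and gives no instruction on which drug to ask about. Appendix C has three statements on medicines in general and two that name none. The six-week medication history shows who uses a RAS inhibitor, but not how faithfully. The answer is no.

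**2. What does a score of at least 4 do?** Five items scored 1 to 5 give 5^5 = 3,125 answer patterns and sums from 5 to 25. The number of patterns that pass (not a forecast of patients) is:

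| Reading | Patterns that pass |
|---|---|
| Sum at least 4 | 3,125 (all) |
| First item at least 4 | 1,250 |
| Mean at least 4 | 247 |
| Sum at least 21 | 126 |
| Every item at least 4 | 32 |

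The two rules in Appendix C also differ. Five fours sum to 20, which passes by item and fails by sum. Of the 126 patterns with a sum of at least 21, 95 contain an item below 4, such as 3+5+5+5+5 = 23. So whether one low answer prompted by another drug removes a patient depends on the reading chosen. Settling the cut-off would still leave the statements about the wrong object.

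**3. Which way does the error go?** Let r be the share of attendees on a RAS inhibitor, a the true share of those who are adherent to it, and Se and Sp the sensitivity and specificity of the general score for RAS-inhibitor adherence. Then

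- true share = r·a
- observed share = r·[a·Se + (1−a)(1−Sp)]
- the error is downward only if a(1−Se) > (1−a)(1−Sp).

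The protocol gives none of the four quantities. All values below are assumptions: r = 0.5, scaled to 112 attendees, so 56 users. Example with a = 0.7, Se = 0.9, Sp = 0.5: true 56 × 0.7 = 39.2; observed 56 × (0.63 + 0.15) = 43.7; difference 4.5/112 = +4.0 points.

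| a | Se | Sp | True n | Observed n | Difference (points) |
|---|---|---|---|---|---|
| 0.9 | 0.8 | 1.0 | 50.4 | 40.3 | −9.0 |
| 0.7 | 0.9 | 1.0 | 39.2 | 35.3 | −3.5 |
| 0.9 | 0.9 | 0.5 | 50.4 | 48.2 | −2.0 |
| 0.8 | 0.9 | 0.5 | 44.8 | 45.9 | +1.0 |
| 0.7 | 0.9 | 0.5 | 39.2 | 43.7 | +4.0 |
| 0.9 | 1.0 | 0.0 | 50.4 | 56.0 | +5.0 |
| 0.7 | 1.0 | 0.0 | 39.2 | 56.0 | +15.0 |

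The last two rows are the sum-score reading, under which every RAS-inhibitor user passes.

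**The case against.** The best defence is that MARS is taken by interview, next to the medication history, and that 9.1.2 links the score to RAS inhibitors. An interviewer could simply ask about that drug. This is possible, but it is not written down. Section 9.3 lets two organisations perform the visits, so practice could differ without anyone noticing.

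Three further points stand and limit the weight of the concern. This is one descriptive secondary endpoint, and Section 11 plans no comparison of it between risk groups. The protocol gives no medication counts, and a single qualifying condition or drug is enough for entry, so the number of patients on several drugs is unknown. The answers are graded, and *seldom* still scores 4, so a rare lapse on another drug need not change the classification.

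A reader might go further and infer that the prevalence is biased low, even attaching a figure. With an assumed 10% chance of poor adherence per medicine, independent across medicines, a faithful RAS-inhibitor user would be wrongly excluded with probability 1 − 0.9^2 = 19% on three medicines and 1 − 0.9^4 = 34% on five, or 0% if adherence is perfectly correlated. The documents do not support that conclusion. The calculation counts only wrongful exclusions, assumes that one poorly taken drug fails the whole score, and rests on inputs that the protocol does not contain. It also presupposes a cut-off that excludes someone, which the sum-score reading does not.

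**Conclusion.** The mismatch is real and can be read directly from the protocol: a criterion specific to one drug class is scored with an instrument about the whole regimen, and no drug-specific administration is stated. RAS-inhibitor users on other drugs can be misclassified both ways.

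The net sign and size cannot be derived from the document. With r = 0.5, a from 0.7 to 0.9, Se of 0.8 or 0.9 and Sp from 0.5 to 1.0, all assumed, the error runs from −9.0 to +4.0 points of the attendees. Under the sum-score reading it runs from +5.0 to +15.0 points. These ranges show that direction is open and are not estimates. The issue touches no primary endpoint, but it should be corrected because it decides who counts in the numerator and the correction is cheap.

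**What to change.** - In Section 9.3 and Appendix C, state that participants using a RAS inhibitor answer the five MARS statements about their ACE inhibitor or ARB, and base secondary endpoint 2 on that score.
- Reconcile the cut-off in the Summary and 9.1.2 with Appendix C. Say whether it is 4 on each item or a sum score of 21, since the two do not select the same patients.
- Report the pilot attendees separately. The 57 examined in the pilot appear to have only the general score. If the 112 includes them, that is 57/112 = 51%, leaving 55 with the drug-specific score.
- For the pilot attendees, add a sensitivity analysis on RAS-inhibitor prescription or dispensing records where the extraction planned in Section 4.3 provides them. That extraction is from general practices and/or pharmacies, so dispensing data are not assured, and a prescription does not prove intake.

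The cost is a wording change on the interview form, with no extra visit or test. The drawback is a split in the endpoint between pilot and extension.
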